## SUMMARY

|                                  |                                                                                                                                                                                                                                                                                                                                                                                                                                                                                                                                                                                                                                                                                                                                                                                                                                                                                                                                                                                                                                                                                 |
|----------------------------------|---------------------------------------------------------------------------------------------------------------------------------------------------------------------------------------------------------------------------------------------------------------------------------------------------------------------------------------------------------------------------------------------------------------------------------------------------------------------------------------------------------------------------------------------------------------------------------------------------------------------------------------------------------------------------------------------------------------------------------------------------------------------------------------------------------------------------------------------------------------------------------------------------------------------------------------------------------------------------------------------------------------------------------------------------------------------------------|
| Title                     | Evaluation of an Educational Program Associated With Exercises (EDEX) Before Total Knee Arthroplasty                                                                                                                                                                                                                                                                                                                                                                                                                                                                                                                                                                                                                                                                                                                                                                                                                                                                                                                                                                            |
| Principal Investigator    | [name] (Cochin Hospital)                                                                                                                                                                                                                                                                                                                                                                                                                                                                                                                                                                                                                                                                                                                                                                                                                                                                                                                                                                                                                                         |
| Research sites            | 
 
- Cochin Hospital
 
- Lariboisière Hospital
 
- Clermont-Ferrand University Hospital
 
                                                                                                                                                                                                                                                                                                                                                                                                                                                                                                                                                                                                                                                                                                                                                                                                                                                                                                                            |
| Study duration            | 60 months (45-month enrolment period)                                                                                                                                                                                                                                                                                                                                                                                                                                                                                                                                                                                                                                                                                                                                                                                                                                                                                                                                                                                                                                           |
| Patient follow-up         | Between 14 and 15 months, depending on the time between the enrolment visit and the intervention for the educational programme combined with an exercise programme                                                                                                                                                                                                                                                                                                                                                                                                                                                                                                                                                                                                                                                                                                                                                                                                                                                                                                              |
| Study aim                 | 
Primary objective:
To assess the effectiveness of a standardised education and exercise programme proposed before a total knee replacement for knee osteoarthritis, in terms of:
 
 
- ability, at discharge from the surgical department at D4, plus or minus 1 day, to carry out lying-sitting and sitting-standing transfers, walk 30 metres and go up and down one flight of stairs;
 
- speed of functional recovery within the first 6 months (area under the curve of the function subscale of the WOMAC index).
 
 
Secondary objectives:
 
 
- to assess the effectiveness of the intervention in terms of pain, function (personalised WOMAC), quality of life, number of steps and treatment satisfaction at 6 and 12 months;
 
- to estimate and compare the cost of the strategies and, where appropriate, carry out a cost-effectiveness analysis.
 
                                                                          |
| Methodology               | A multi-centre, randomised, controlled study                                                                                                                                                                                                                                                                                                                                                                                                                                                                                                                                                                                                                                                                                                                                                                                                                                                                                                                                                                                                                                    |
| Number of sites           | 3 sites                                                                                                                                                                                                                                                                                                                                                                                                                                                                                                                                                                                                                                                                                                                                                                                                                                                                                                                                                                                                                                                                         |
| Number of patients        | 
300 patients will be enrolled:
150 patients in the experimental arm
150 patients in the control arm (usual information and advice given by the surgeon)
                                                                                                                                                                                                                                                                                                                                                                                                                                                                                                                                                                                                                                                                                                                                                                                                                                                                                                   |
| Selection criteria        | 
Inclusion criteria:
 
 
- Men or women aged from 50 to 85 years;
 
- Patients with knee osteoarthritis according to the ACR criteria for which a total knee arthroplasty has been scheduled by the surgeon;
 
- Medical examination carried out in advance, the results of which will be communicated to the patient;
 
- Patients having provided their written informed consent to take part in the study;
 
- Patients affiliated with a social security scheme (beneficiary or entitled party).
 
 
Exclusion criteria:
 
 
- Institutionalised patients;
 
- Patients having already undergone ipsilateral total knee arthroplasty;
 
- Patients with chronic inflammatory arthritis;
 
- Cognitive or behavioural disorders making the assessment impossible;
 
- Difficulties in understanding and communicating in French;
 
- TKA for an indication other than knee osteoarthritis.
 
 |
| Early withdrawal criteria | 
 
- Failure to meet the eligibility criteria
 
- The onset during the study of a condition listed in the exclusion criteria
 
                                                                                                                                                                                                                                                                                                                                                                                                                                                                                                                                                                                                                                                                                                                                                                                                                                                                                              |

|                                        |                                                                                                                                                                                                                                                                                                                                                                                                                                                                                                                                                                                                                                                                                                                                                                                                                                                                                                                                                                      |
|----------------------------------------|----------------------------------------------------------------------------------------------------------------------------------------------------------------------------------------------------------------------------------------------------------------------------------------------------------------------------------------------------------------------------------------------------------------------------------------------------------------------------------------------------------------------------------------------------------------------------------------------------------------------------------------------------------------------------------------------------------------------------------------------------------------------------------------------------------------------------------------------------------------------------------------------------------------------------------------------------------------------|
| Study treatment                 | 4 group sessions consisting of a therapeutic education session and a physical exercise programme                                                                                                                                                                                                                                                                                                                                                                                                                                                                                                                                                                                                                                                                                                                                                                                                                                                                     |
| Study outline                   | 
 
- Enrolment visit (V0);
 
- Intervention (education programme combined with an exercise programme);
 
- Preoperative visit;
 
- Surgery department discharge visit (medical record information);
 
- Monthly follow-up by post or email in terms of function (and personalised) subscale of the WOMAC index and pain in the past 48 hours, 6 weeks after surgery, 4 and 5 months after surgery, and 6 months after surgery with a self-questionnaire.
 
 
Postoperative self-questionnaires at 3 and 12 months, according to the patient's preference:
 
 
- Self-questionnaires given at a consultation;
 
- or self-questionnaires will be sent by post (prepaid envelope);
 
- or self-questionnaire information can be collected by a clinical study technician by phone.
 
                                    |
| Primary and secondary endpoints | 
Primary endpoints
 
 
- Ability at discharge: Assessed at D4, plus or minus 1 day. The endpoints to be assessed will be the ability to carry out lying-sitting and sitting-standing transfers, walk 30 metres and go up and down one flight of stairs (percentage of patients with a score of 3 out of 3 for the 4 items on the day of discharge);
 
- Speed of postoperative functional recovery at 6 months (area under the curve of the function subscale of the WOMAC index).
 
 
Secondary endpoints
 
 
- Pain assessment (numeric scale), function (personalised WOMAC index), quality of life (MOS SF-12, EQ-5D-3L), number of steps and treatment satisfaction;
 
- Cost comparison between the two strategies from the Health Insurance perspective and from the care system perspective, as a cost-effectiveness ratio.
 
 |
| Statistical analysis            | 
An intention-to-treat analysis will be carried out with the data.
 
The statistical analysis will be carried out at the [name] Clinical Ethics Centre - Hôtel Dieu hospital, under the responsibility of [name] and [name]. SAS software will be used.
                                                                                                                                                                                                                                                                                                                                                                                                                                                                                                                                                                                                                                                                               |

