## **IV.2 - EXCLUSION CRITERIA**

- Institutionalised patients;
- Patients having already undergone ipsilateral total knee arthroplasty;
- Patients with chronic inflammatory arthritis;
- Cognitive or behavioural disorders making the assessment impossible;
- Difficulties in understanding and communicating in French;
- TKA for an indication other than knee osteoarthritis.

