#### **VII.4 - EXITING THE TRIAL AND EARLY WITHDRAWAL**

Patients may leave the study at any time and for any reason, if they decide to do so. This will have no consequences on the quality of any subsequent care that the patient will receive. Patients may also be withdrawn from the trial at the investigator's discretion. All cases of patients withdrawing from the study must be documented.

In the event of early withdrawal, the investigator must fill in the case report form up to the date of early withdrawal. The reason for the early withdrawal must be specified. Patients withdrawing from the trial cannot be enrolled again in the study. The patient's treatment will continue in the context of routine care.

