## **IX.3 - ANALYSIS STRATEGY FOR COLLECTED DATA**

An intention-to-treat analysis will be carried out. All randomised patients will be analysed and each patient will be analysed in the group to which they have been randomised, regardless of the technique received.

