#### 3.2 Analysis populations definition

**Intention-to-treat (ITT):** this population includes all patients randomised into the trial. The patients are analysed in the group to which they were randomised, regardless of the treatment received and regardless of any protocol deviations.

No data will be analysed for patients for whom a signed informed consent form was not collected or for patients who withdrew their consent to use their data during the course of the study. The data concerning these patients, if any have been collected, will be destroyed. The presence of any such patients will be documented in the study flow chart.

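### Withdrawal rules let outcome collection stop for randomised patients whom the ITT analysis keeps, so some outcomes go missing avoidably

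*Supplement*

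**What the plan says.** The current protocol (v5.0) gives two early-withdrawal criteria in its Summary: "Failure to meet the eligibility criteria" and "The onset during the study of a condition listed in the exclusion criteria". SAP v2.0 carries both over in section 2. Protocol VII.4 adds a discretionary route, "Patients may also be withdrawn from the trial at the investigator's discretion", and sets how much is recorded: "In the event of early withdrawal, the investigator must fill in the case report form up to the date of early withdrawal". VII.4 does not ask for outcomes after that date. The reminders in VII.5 are for patients who miss a consultation or cannot be reached; they do not mention withdrawn patients.

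On the analysis side, protocol IX.3 states "All randomised patients will be analysed and each patient will be analysed in the group to which they have been randomised". SAP 3.2 agrees: "this population includes all patients randomised into the trial", "regardless of the treatment received and regardless of any protocol deviations". It sets aside only patients without signed consent or who withdrew consent to the use of their data. SAP 3.1 reports patients found ineligible after randomisation in the flow chart.

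SAP 4.4 imputes missing primary endpoints by chained equations, separately by arm, from baseline characteristics and the two primary endpoints. Secondary endpoints are left to mixed models without imputation. SAP 5.1.3 and 5.2.3 offer one missing-data check, the analysis without imputation.

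**The concern.** The analysis needs an outcome for everyone randomised, while the conduct rules let collection stop for some of them for reasons that arise or come to light after randomisation. At least one trigger, becoming institutionalised, is plausibly linked to poor function. If such patients leave follow-up, their later WOMAC scores are absent. The imputation model names neither the reason for withdrawal nor the WOMAC scores collected before it.

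The rules could also bite unequally. Only the experimental arm has four extra supervised contacts at which ineligibility or a new condition might be noticed, and the care team is not blinded. That is a judgement; the documents give no rates. At stake is some loss of precision and a possible bias that continued collection at scheduled contacts would largely avoid.

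**Working it through.** The plan gives no withdrawal rate, so the main check is textual and the arithmetic only sizes the point.

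**1. What each trigger would cost** (protocol IV.2, assessment schedule in VII)

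- *Found ineligible after randomisation.* This could occur early and lose every later outcome. III.4 has eligibility confirmed before randomisation, so cases should be few.
- *Institutionalised.* This can arise after surgery. WOMAC is due at 6 weeks and at months 3, 4, 5, 6 and 12; contacts after withdrawal are lost.
- *Chronic inflammatory arthritis.* This can arise at any time, and questionnaires remain possible.
- *Cognitive or behavioural disorder.* The criterion is limited to disorders that make assessment impossible, so continued collection recovers little.
- *Language difficulty, prior ipsilateral arthroplasty, another indication.* These describe status at enrolment and matter only as ineligibility discovered late.

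Discharge ability is taken from D5, D4 or D3 (SAP 5.1.1), so it is lost only if withdrawal comes earlier. Protocol IX.4 has a different rule for a missing area under the curve (a value of 1). That mismatch is a separate matter; the SAP's imputation is assumed here.

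**2. The plan's own figure for the WOMAC endpoint** (protocol IX.2: 130 per arm, effect 0.45, two-sided 2.5%, Mann-Whitney)

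Power = Φ(0.45 × √(0.955n/2) − 2.241), where 0.955 is the relative efficiency of the Mann-Whitney test under normality. At n = 130 this is Φ(3.545 − 2.241) = 90.4%. The stated 90% reproduces.

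**3. Precision.** Take 150 per arm and 10% loss before surgery (both from IX.2), then an assumed further share withdrawn without this outcome, treated as lost information:

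| Further withdrawal (assumed) | n per arm | Power |
|---|---|---|
| 0% | 135 | 91.5% |
| 2% | 132 | 90.8% |
| 5% | 127.5 | 89.8% |
| 10% | 120 | 87.8% |

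**4. Bias on the WOMAC endpoint.** If withdrawn patients are imputed like those who stayed in their arm, bias in the difference = (between-arm imbalance in withdrawal) × (gap in score). Assume an imbalance of 2 to 3 percentage points, a gap of 20 to 30 points on the 0-100 scale, and an SD of 20:

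- low: 0.02 × 20 = 0.4 points; 0.4/20 = 0.02 SD
- high: 0.03 × 30 = 0.9 points; 0.9/20 = 0.045 SD

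Against the planned 0.45 this is 4% to 10%. The standard error of the difference at 130 per arm is √(2/130) = 0.124 SD, so the bias is 16% to 36% of one standard error. The range probably overstates the effect, because it applies a 6-month gap to an area that, per protocol IX.4, starts at enrolment. A 3-point imbalance also needs more than 1% withdrawn overall: 1% is 3 of 300, at most 3/150 = 2% against 0%.

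**5. Bias on discharge ability.** Suppose the withdrawals come before D3, all those patients are in truth not independent, and each is imputed at the observed rate of their arm. With a true 20% in both arms:

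- 10% v 5% withdrawn: 0.20/0.90 − 0.20/0.95 = +1.2 points
- 10% v 2% withdrawn: 0.20/0.90 − 0.20/0.98 = +1.8 points
- 5% v 5% withdrawn: 0

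These are extreme settings for so short a window.

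**The case against.** The strongest reply is that the plan already handles these patients. SAP 3.2 keeps them, 3.1 reports the ineligible, and 4.4 imputes within arm, using observed discharge ability to inform a missing WOMAC area. VII.4 states what must be recorded; it does not forbid later collection. Nor is transfer to rehabilitation treated as an exit, since VII.3.3, VII.3.4 and VII.3.6 collect length of stay there. The affected group may therefore be very small, and no document shows that its withdrawals differ by arm.

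Most of this stands and limits the point. What it does not supply is any instruction to keep collecting. A site that follows VII.4 as written may stop, and imputation then replaces data that could have been observed.

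Three stronger readings are tempting, and the documents do not support them:

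- *The rules contradict intention to treat.* They do not. Protocol IX.3 and SAP 3.2 both define the set as everyone randomised; a missing outcome is not an exclusion.
- *Outcome-related patients are removed from the analysis.* They leave follow-up, not the analysis set.
- *Every operated patient acquires an exclusion condition.* The criterion reads "Patients having already undergone ipsilateral total knee arthroplasty", which describes history at enrolment. The index operation is the scheduled study event, with follow-up planned to 12 months after it.

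**Conclusion.** The point holds as a matter of avoidable missing data. The withdrawal criteria and VII.4 together allow outcome collection to end for randomised patients whose outcomes the analysis still needs, and no section provides otherwise. The main exposure is the 6-month WOMAC area and the secondary endpoints.

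The effect is probably small. The illustrative bias of 0.02 to 0.045 SD rests wholly on an assumed imbalance, gap and SD. An assumed 5% further withdrawal costs under 2 points of power (91.5% to 89.8%). Neither the true size nor the direction can be derived from the documents. This is a minor improvement, worth making because it is cheap.

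**What to change.** In the protocol Summary, in VII.4 and in the SAP's protocol summary, add wording such as: *Patients found ineligible after randomisation, or who develop a listed condition, remain in follow-up. Discharge ability and all scheduled questionnaires continue to be collected where assessment is possible, unless the patient withdraws consent.*

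This concerns data collection only and leaves decisions about the sessions as they are. The cost is wording in three places and a few extra questionnaires at contacts already scheduled. Some data will still be missing where a cognitive or behavioural disorder makes assessment impossible.
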